### Biomaterials

Three types of biomaterials are collected: blood, urine and AAA tissue (table 4).

**Table 4 T4:** Biomaterials collected for the AAA bank

Biomaterials	Inclusion	Surveillance phase	Surgical phase	Postoperative phase	Storage temperature
Blood: EDTA plasma	Once	Max. 1/year	Once	Once: 1 year postoperative	≤−80°C
Blood: serum	Once	Max. 1/year	Once	Once: 1 year postoperative	≤−80°C
Blood: citrate plasma	Once	Max. 1/year	Once	Once: 1 year postoperative	≤−80°C
Blood: EDTA for DNA	Once				4°C or ≤−20°C
Blood: PAXgene for RNA	Once				≤−80°C
Urine	Once	Max. 1/year	Once	Once: 1 year postoperative	≤−80°C
Aneurysm tissue: frozen			Once		≤−80°C
Aneurysm tissue: FFPE			Once		Room temperature

FFPE, formalin-fixed paraffin-embedded.

Blood and urine are collected repeatedly during the surveillance phase, up to a maximum of once per year to limit patient burden. Blood is saved as plasma, serum and whole blood for DNA and RNA. When open surgical repair of AAA is performed, aortic tissue is collected, snap frozen and stored at −80°C, and as formalin-fixed paraffin-embedded tissue. After surgery for AAA, blood and urine are collected up to 1 year postoperatively (table 4). All procedures concerning biomaterials adhere to standard operating procedures outlined by PSI. Furthermore, all biomaterials are stored in designated PSI biobanks within each UMC. Thus, all biomaterials are stored in the UMC where they are collected.

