### Statistical analyses

The primary outcomes are AAA growth, AAA rupture and all-cause mortality. AAA growth will be based on multiple measurements and will therefore be analysed with a repeated measures analysis. Potential associations between AAA growth and risk factors that are also measured on multiple time points can be assessed with multivariable mixed-effects models, while potential associations between AAA rupture and risk factors can be tested with a conditional dynamic prediction model with landmarking, or with joint models in which linear mixed-effects models are combined with Cox regression.

Due to the expected multifactorial aspect of AAA growth, even weak correlations are of interest to detect. To that end, at least 750 patients are required to be able to detect a correlation coefficient of 0.16 with a power of 80% and a significance level of 0.05.

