## Ethics and dissemination

The Medical Ethics Board and the Biobank Ethics Board of Amsterdam UMC (University of Amsterdam) have approved the AAA bank together with the PARIS study (table 5) within the scope of the Dutch Medical Research Involving Human Subjects Act (WMO) under registration number NL59991.018.17.

**Table 5 T5:** The PARIS study, the first proposed study that will be facilitated by the AAA bank

Aims	The aims of the PARIS study are: (1) to determine the association between AAA progression (growth or rupture) and the evolution of serum levels of both proteases and cytokines, (2) to determine the association between overall survival and the evolution of serum levels of proteases and cytokines, (3) to determine the association between serum levels of proteases and cytokines and level of proteases and cytokines in AAA tissue and finally (4) to determine the incidence of and characterise the type of complications after AAA repair.
Outcomes	The primary outcomes are: AAA growth, AAA rupture, all-cause mortality, serum levels of cytokines and proteases and cytokine and protease levels in AAA tissue. Secondary outcomes are the incidence and type of complications after AAA repair.
Sample size	Because of the multifactorial aspect of AAA progression, we calculated a sample size that will be sufficient for detecting weak correlations between cytokine and protease levels and AAA growth. To detect a correlation coefficient of 0.16 with a power of 80%, and a significance level of. 05, a sample size of 750 participants is required. Strategies to achieve sufficient participant enrolment include simple eligibility criteria and the expressed intention to extend the number of participating centres.

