Statistical analysis	Categorical variables will be presented as numbers and percentages and will be compared between groups with the χ^2^ test of Fisher’s exact test where appropriate. Continuous variables will be presented as means±SD or as medians with the IQR, depending on distribution. Distribution of continuous variables will be tested with the Shapiro-Wilk test. Continuous variables will be compared between groups with either the unpaired t-test or the Mann-Whitney U test depending on distribution. Individual AAA growth (based on repeated AAA diameter measurements) and the evolution of serum levels of cytokines and proteases will each be analysed with linear mixed-effects models to estimate the slope of temporal change (ie, the evolution through time). The linear mixed-effects model that estimates the slope for the evolution of each biomarker will also adjust for potentially relevant covariables including but not limited to sex, age and cardiovascular comorbidity. A forward stepwise selection will be used to select only those covariables that were significant in univariable analysis. Finally, correlations coefficient will be estimated between the slope of AAA progression and the slope of each biomarker. Freedom from AAA rupture and all-cause mortality will be estimated with the Kaplan-Meier method, while joint modelling will be used to assess the association between the evolution of serum levels of proteases and cytokines and AAA rupture and all-cause mortality. A joint model will be performed per biomarker. In order to assess the association, joint modelling combines linear mixed-effects models for the estimation of slope of temporal change per biomarker with Cox regression for the analysis of freedom from AAA rupture and all-cause mortality, in order to estimate HRs. The estimated slope and value of the studied biomarker will be added as covariables in each joint model. Furthermore, both models will be adjusted for potentially relevant covariables, including but not limited to sex, age, most recent AAA diameter and cardiovascular comorbidity using the same selection procedure. In addition, AAA growth instead of the most recent AAA diameter will be analysed in a separate multivariable joint model. In all analyses, a p value of <0.05 will be considered statistically significant, including the covariable selection procedure.

AAA, abdominal aortic aneurysm; PARIS, Predicting aneurysm growth and rupture with longitudinal biomarkers.

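### Correlating slopes from separate mixed models biases the PARIS growth-biomarker correlation towards zero, and its ordinary confidence interval under-covers

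*Protocol article*

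**What the plan says.** Table 5 of the protocol article (under Ethics and dissemination, row on statistical analysis) sets out the growth analysis of the PARIS study in two steps. Diameter and biomarker levels "will each be analysed with linear mixed-effects models to estimate the slope of temporal change". The slopes are then related to each other: "Finally, correlations coefficient will be estimated between the slope of AAA progression and the slope of each biomarker".

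The models are separate. Covariate adjustment before the correlation step is described for the biomarker side only: "The linear mixed-effects model that estimates the slope for the evolution of each biomarker will also adjust for potentially relevant covariables". Joint models are planned per biomarker, but for rupture and mortality, not for growth.

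The data behind each slope are limited. The Biomaterials section has blood and urine taken during surveillance "up to a maximum of once per year to limit patient burden". The strengths and limitations list says that follow-up will vary between patients, and Study procedures ties visit intervals to diameter.

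The sample size row of Table 5 reads "To detect a correlation coefficient of 0.16 with a power of 80" per cent at a significance level of 0.05, and concludes that "a sample size of 750 participants is required". The Statistical analyses section repeats the inputs and adds that weak correlations matter.

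**The concern.** A slope predicted from a mixed model is an estimate, shrunk towards the mean by an amount that depends on how many measurements the patient has. The second step treats these predictions as data. If the two series are modelled separately, the error in each set of slopes is unrelated to the other set. The correlation between them is then closer to zero than the correlation between the underlying slopes, which is what the first PARIS aim asks about. A confidence interval computed in the usual way is centred on the attenuated quantity and does not allow for the error in the slopes.

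At stake are the reported size of every growth-biomarker association, the honesty of its interval, and some power, in a study that says it looks for weak correlations.

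**Working it through.** **1. The plan's own figure.** Inputs from Table 5: r = 0.16, power 80%, alpha 0.05 (taken as two-sided; sidedness is not stated). Fisher z: N = ((1.960 + 0.842) / atanh(0.16))² + 3 = (2.802 / 0.1614)² + 3, which rounds up to 305. The stated 750 is not reproduced. At N = 750, power for 0.16 is 99.3%, and 80% power is reached at r = 0.102. So there is a surplus, for which the article gives no reason.

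**2. Attenuation and power.** Expected observed correlation: r_obs ≈ r_true × g, where g = sqrt(R_growth × R_biomarker) is the geometric mean of the two slope reliabilities. With r_true = 0.16 and two-sided alpha 0.05:

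| g | r_obs | Power at 750 | N for 80% |
|---|---|---|---|
| 1.0 | 0.160 | 99% | 305 |
| 0.8 | 0.128 | 94% | 477 |
| 0.6 | 0.096 | 75% | 850 |
| 0.5 | 0.080 | 59% | 1225 |
| 0.4 | 0.064 | 42% | 1914 |

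The break-even for 80% power at 750 is g = 0.102 / 0.16 ≈ 0.64.

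**3. What g might be.** The documents give no slope or error variances, so these are assumptions: growth SD 1.5 mm/year, diameter error SD 2.5 mm, biomarker slope SD 0.15 and error SD 0.5 (in baseline-SD units). For m yearly visits, R = qS / (1 + qS), with S = m(m² − 1)/12 and q = slope variance / error variance. Growth: q = 2.25/6.25 = 0.36. Biomarker: q = 0.0225/0.25 = 0.09.

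| Visits | S | R growth | R biomarker | g | 0.16 × g |
|---|---|---|---|---|---|
| 3 | 2 | 0.42 | 0.15 | 0.25 | 0.040 |
| 5 | 10 | 0.78 | 0.47 | 0.61 | 0.097 |
| 7 | 28 | 0.91 | 0.72 | 0.81 | 0.129 |
| 11 | 110 | 0.98 | 0.91 | 0.94 | 0.151 |

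**4. Simulation of the planned two steps.** n = 750, true r = 0.16, the variances above, baseline diameter 42 mm (SD 6), mean growth 2.2 mm/year, yearly visits; exit, where applied, at the first observed diameter of 55 mm or more.

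| Series | Exit | Mean visits | Mean r | Rejection | Coverage of nominal 95% CI |
|---|---|---|---|---|---|
| up to 5 years | no | 4.5 | 0.090 | 70% | 49% |
| up to 5 years | yes | 4.1 | 0.085 | 67% | 45% |
| up to 10 years | no | 7.0 | 0.125 | 93% | 80% |
| up to 10 years | yes | 5.5 | 0.102 | 79% | 63% |

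The rows without exit agree with step 3. With a true correlation of zero, the rejection rate was 5-7% (300 runs per setting). A second simulation varied diameter error SD over 2-3 mm and biomarker slope reliability over 0.16-0.73, with 3.7-5.1 measurements on average and 60 runs per scenario. It gave mean r from 0.05 to 0.13 and rejection from about 23% to 95%.

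**5. Separating exit from sparse data.** Comparing exit with no exit mixes two effects. Keeping the same exit times but permuting them across patients isolates the part due to dependence on diameter. Two such checks gave, for diameter-driven against permuted exit, 0.105 against 0.109 and 0.100 against 0.113 (up to 5 years), and 0.130 against 0.130 and 0.116 against 0.126 (up to 10 years). The first figure in each pair of checks treats the variance components as known. The extra bias is thus 0 to 0.013; most of the loss comes from shorter series.

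**6. The alternative.** A bivariate mixed model on simulated data with exit (40 runs per setting) estimated a true 0.16 as 0.156 (SE 0.012, up to 5 years) and 0.155 (SE 0.008, up to 10 years). The two-step method on the same data gave 0.081 and 0.097. For a true 0.50 the bivariate model gave 0.51 in both settings, against 0.26 and 0.33.

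**The case against.** The best defence is the surplus in N. With 305 needed and 750 planned, power survives attenuation down to g of about 0.64. This stands for power, with two limits. The article does not present the surplus as an allowance for slope error. It also counts all 750, although the Study population section admits previously repaired and acute patients, who may contribute no pre-repair growth slope. A larger N does nothing for the bias, and it narrows the interval around the wrong value.

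Four stronger readings are tempting, and the documents or the calculations do not support them:

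- **False positives.** A reader might infer that ignoring slope error invalidates the p-value. The rejection rate under zero correlation was 5-7%, so the test is close to nominal.
- **Equal weighting.** A reader might think that a patient with two samples counts as much as one with ten. Table 5 specifies mixed models, and shrinkage already pulls sparse patients to the mean, so they add little to the correlation.
- **Exit as a separate major flaw.** Step 5 shows only a small extra bias. Mean growth also stayed unbiased under exit (2.19-2.20 against a true 2.2 mm/year).
- **A sample size that assumes error-free slopes.** Table 5 words the target correlation in terms of biomarker levels and growth, and does not say whether 0.16 is a true or an observable value.

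It can also be said that the Statistical analyses section allows multivariable mixed models for growth with repeated risk factors, and that the full protocol is not shown. The first is optional wording for the bank as a whole, and Table 5 does not carry it into PARIS. The second could supply detail on intervals, but the two-step method itself is stated.

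**Conclusion.** The point holds as a choice of method that should be changed. As written, the PARIS growth analysis gives a correlation biased towards zero by a factor of about g, at every true value and not only for weak correlations, with an interval that under-covers the true slope correlation. The direction follows from the method and from sparse, variable follow-up. The size does not come from the documents: 0.05 to 0.13 for a true 0.16, and coverage of 45-63% with exit, are illustrations under the assumed variances, yearly visits and a 55 mm exit. With long series and a precise assay the loss would be modest. It cannot be concluded that the study is underpowered, since that depends on g and on how many of the 750 contribute pre-repair slopes.

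**What to change.** For each biomarker, fit one bivariate linear mixed model of diameter and biomarker with correlated random intercepts and slopes, using pre-repair (surveillance) measurements only. The restriction is needed because previously repaired and acute patients are enrolled and a one-year postoperative sample is collected (Table 4). Report the random-slope correlation with its likelihood-based confidence interval as the main growth-biomarker estimate, and keep the two-step correlation as descriptive.

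This removes the attenuation and makes exit ignorable where it depends on recorded diameters, provided the model is adequate. It does not cover exit for unrecorded reasons, and it does not restore information lost to sparse sampling, so intervals may be wide.

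Cost: a change of analysis wording, somewhat more computing, and occasional convergence problems with sparsely measured biomarkers. No new visits or data are needed, and the plan already commits to a joint model per biomarker for rupture and mortality. Table 1 reports 161 of 750 enrolled, so the change can be made well before analysis.

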## Introduction

An abdominal aortic aneurysm (AAA) is a focal dilatation of the abdominal aorta that affects mostly elderly men. The prevalence of AAA in the general population is 1.3%–2.2% in 65-year-old men.^1 2^ An AAA is an asymptomatic disorder that is associated with a high risk of mortality in case of rupture.^3^ Yet, the risk of rupture itself is difficult to measure accurately and also varies considerably between patients. Consequently, the management of patients with an asymptomatic AAA is focused on balancing the risk of rupture with other competing risks of death, with the aim of preserving quality and quantity of life. On the one hand, asymptomatic patients who are estimated to have a high risk of rupture, in general at a diameter of more than 5.5 cm for men, may be offered prophylactic AAA repair if the risk of rupture outweighs any procedural and/or competing risks.^4^ On the other hand, asymptomatic patients for whom the risk of rupture is estimated to be smaller than procedural and/or competing risks will be offered surveillance, for example, those with an AAA diameter smaller than 5.5 cm or those with severe comorbidities. A large body of research has been dedicated to determining the optimal surgical treatment for AAA, focusing on either the threshold diameter for repair, the method of repair or the outcome and follow-up after treatment.

Although many studies have tried to unravel AAA pathophysiology, this aspect is still insufficiently understood. Most of the current knowledge originates from histopathological studies that reflect the end stage of AAA disease. Early determinants and drivers of AAA formation are largely unidentified due to the unavailability of AAA tissue from an early stage of the disease. Therefore, the known determinants of AAA development are limited to general risk factors such as male sex, ageing, smoking or connective tissue diseases.^5 6^

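### Kaplan-Meier for freedom from AAA rupture overstates the actual probability of rupture, because death competes with rupture and the handling of repair is not stated

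*Protocol article*

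**What the plan says.** The statistical analysis row of Table 5 (PARIS study) in the protocol article names the estimator for the event curves: "Freedom from AAA rupture and all-cause mortality will be estimated with the Kaplan-Meier method". For the association with biomarkers, the same row specifies one joint model per biomarker, combining a linear mixed-effects model "with Cox regression for the analysis of freedom from AAA rupture and all-cause mortality, in order to estimate HRs". The biomarker's value and slope enter as covariables, and "both models will be adjusted for potentially relevant covariables, including but not limited to sex, age, most recent AAA diameter and cardiovascular comorbidity", subject to stepwise selection at p<0.05. The main Statistical analyses section is broader. It allows rupture to be studied "with a conditional dynamic prediction model with landmarking, or with joint models in which linear mixed-effects models are combined with Cox regression".

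The Introduction describes management as "balancing the risk of rupture with other competing risks of death". It says that patients judged to be at high risk of rupture, "in general at a diameter of more than 5.5 cm for men, may be offered prophylactic AAA repair".

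Table 1, the Statistical analyses section and Table 5 all list rupture and all-cause mortality as separate primary outcomes, and Table 1 gives a horizon of up to 10 years. Under Study population, previously repaired patients are eligible. The article names no cumulative incidence function and no competing-risks method, and gives no rule for what happens to the rupture analysis at death or at repair.

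**The concern.** A patient who dies without rupture can no longer rupture. Kaplan-Meier treats that patient as censored, as if still able to rupture later at the same rate as those who remain. The complement of the curve is then larger than the proportion of patients who rupture.

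Repair raises a second problem. It is offered because rupture risk is judged high. If follow-up for rupture is censored at repair, the patients removed are those with the larger aneurysms, and those who remain do not represent them. The curve then gives neither the risk under current care nor the risk had nobody been repaired. If follow-up is not censored at repair, the curve mixes repaired and unrepaired aneurysms.

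Better knowledge of rupture risk is one of the bank's three scientific aims, and PARIS is the first study to use the bank. An absolute rupture figure from this curve could be read as the probability of rupture in a surveillance cohort.

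**Working it through.** **Inputs.** From the article: Kaplan-Meier for rupture (Table 5), a horizon of up to 10 years (Table 1), death as a competing risk and diameter-related repair (Introduction). The article states no rupture, death or repair rate, so there is no figure of its own to reproduce. All rates below are assumptions: rupture 0.5%, 1% or 3% per year; death 3%, 5% or 8% per year; repair 0%, 5% or 15% per year.

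**Step 1: difference between the two quantities, constant hazards.** Write h for the rupture hazard, d for death, p for repair and t for time.

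- 1-KM with death and repair censored: 1 - exp(-h·t)
- Cumulative incidence of rupture: h/(h+d+p) × [1 - exp(-(h+d+p)·t)]

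Worked example with h = 0.01, d = 0.05, t = 10:

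- 1-KM = 1 - exp(-0.10) = 9.5%
- Death as the only competing event (p = 0): 0.01/0.06 × [1 - exp(-0.60)] = 7.5%, ratio 1.27
- With p = 0.05: 0.01/0.11 × [1 - exp(-1.10)] = 6.1%, ratio 1.57
- With p = 0.15: 0.01/0.21 × [1 - exp(-2.10)] = 4.2%, ratio 2.28

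Ratio of 1-KM to cumulative incidence at 10 years over the whole grid:

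| Competing events | Lowest | Highest |
|---|---|---|
| Death only | 1.15 | 1.45 |
| Death, repair 5%/yr | 1.42 | 1.78 |
| Death, repair 15%/yr | 2.07 | 2.53 |

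The death-only extremes are:

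- h = 0.03, d = 0.03: 25.9% against 22.6%
- h = 0.005, d = 0.08: 4.9% against 3.4%

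In this step the hazards are independent, so 1-KM equals the net risk exactly. The ratios show a difference of estimand and do not demonstrate informative censoring.

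**Step 2: informative censoring at repair, by simulation.** The assumptions for 200,000 patients over 10 years in steps of 0.1 year were:

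- baseline diameter uniform on 3.0-5.4 cm
- growth normal with mean 0.25 and SD 0.15 cm per year, not below zero
- rupture hazard 0.001 × exp(1.2 × (diameter - 3)) per year
- death 5% per year, independent of diameter
- once diameter reaches 5.5 cm, a repair probability of 0, 0.1 or 0.3 per step

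| Repair probability per step | 1-KM | Cumulative incidence |
|---|---|---|
| 0 | 34.7% | 24.8% |
| 0.1 | 10.7% | 5.4% |
| 0.3 | 8.8% | 4.2% |

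The rupture risk with neither death nor repair, computed directly under the same assumptions, is 34.8%. With repair switched off, 1-KM recovers it (34.7%). With diameter-triggered repair censored, 1-KM falls to about 9-11%. That is well below the no-repair risk and still about twice the probability of rupture before repair.

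**The case against.** **The quoted sentence could describe a composite.** Freedom from rupture and death combined would remove death as a competing event. The article does not favour that reading: the two are separate primary outcomes, and PARIS aims 1 and 2 separate them. A composite would also leave repair unaddressed.

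**The article is condensed, and censoring at repair is nowhere stated.** This stands. Previously repaired patients are eligible and follow-up continues in a postoperative phase, so repaired patients may remain at risk in the analysis. The larger ratios and the downward bias for no-repair risk therefore hold only if repair is censored. The death part does not depend on this, because the estimator is named and censors deaths.

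**A reader might infer that the regression is a plain Cox model with invalid rupture hazard ratios.** The documents do not support that. Cox is the event part of a joint model with biomarker value and slope. Censoring deaths there gives a cause-specific hazard ratio, which is legitimate for association. Conditioning on current diameter also makes repair less informative, although stepwise selection decides whether diameter is kept.

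**A reader might infer that rupture risk is simply overstated.** That is true for the actual probability of rupture. For natural history without repair the bias runs the other way, and natural history is also among the bank's aims.

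**A reader might infer that death and repair leave the biomarker trajectories wholly unmodelled.** That also goes too far. Table 5 specifies a joint analysis with all-cause mortality as well, and Table 4 schedules sampling at surgery and one year afterwards.

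**The curve is descriptive.** This stands and lowers the severity. The PARIS aims concern associations of biomarkers with growth, rupture and survival, and none is to estimate absolute rupture risk. Later studies from the bank must submit their own analysis plans.

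**Conclusion.** The point holds for the absolute-risk estimate. Followed as written, Table 5 yields a rupture curve whose complement exceeds the actual probability of rupture. With death as the only competing event the 10-year excess is about 1.15 to 1.45 times under the assumed rates. It rises to about 2.5 times if repair at an assumed 15% per year is also censored. If repair is censored, the curve is not a valid no-repair risk either, and for that target it is too low. The direction of bias therefore depends on which rupture risk is meant, and the article does not say.

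Every size given here rests on assumed rates, and the simulation also rests on assumed growth and on an assumed relation between diameter and rupture. The existence of the death effect needs only that some patients die without rupture. Severity is moderate: a primary outcome is affected, but in a descriptive estimate beside aims that are mainly associations.

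**What to change.** 1. State the rupture estimand and its risk set, including how already repaired aneurysms and rupture after repair are treated.
2. Report rupture with the Aalen-Johansen cumulative incidence function, with death without rupture as a competing event. If the estimand is rupture before repair, make elective repair a competing event too. This answers the question under current care; it does not give a natural-history risk without repair.
3. Keep Kaplan-Meier for all-cause mortality only.
4. Label the rupture hazard ratios from the joint model as cause-specific, and keep current AAA diameter in the rupture model regardless of the stepwise result.

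The cost is a few sentences in the plan, a little more analysis work with standard software, and a different absolute-risk figure. No new data are needed: Table 3 already includes date and type of repair and survival status with cause of death, and mortality can be traced for patients who leave surveillance. Recruitment was under way with no results at the time of writing, so the change could be made before any rupture analysis.

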### Study procedures

The study procedures of the AAA bank are embedded within regular AAA treatment and are carried out by physician-researchers and data managers. Standard operating procedures have been set up to minimise the amount of missing data. Clinical data and biomaterials are collected during and after visits that are already part of clinical treatment to limit participant burden and improve participant retention. No research visits will be planned for the AAA bank. In addition, only imaging data that is obtained as part of clinical care will be stored in the AAA bank.

In line with regular AAA management, four distinct study phases have been identified: inclusion phase, surveillance phase, surgical phase and postoperative phase (figure 1; blue boxes). Within each phase, multiple visits can take place—especially in the surveillance or postoperative phase. These phases can theoretically continue indefinitely, depending on the course of the AAA. With regard to the ‘surveillance phase’, the Dutch AAA guideline advises that patients visit a vascular surgeon at intervals of 2 years, 1 year or 3 months, depending on the AAA diameter.^19^ Patients can move from the ‘surveillance phase’ to the ‘surgical phase’ and subsequently to the ‘postoperative phase’ (figure 1). Furthermore, there will be patients who at some point reach the threshold diameter for repair yet who do not undergo repair for various reasons such as severe comorbidity. In these cases, an individual clinical decision—unrelated to their participation with the AAA bank—will have to be made together with the patient whether surveillance continues with regular intervals or whether the patient chooses to quit with surveillance altogether. Patients who choose to continue with surveillance will still be asked for biomaterials and clinical data, while patients who quit surveillance can be analysed using the previously collected data up until that moment. Furthermore, the latter patients can also be included in survival analyses as mortality data can be sourced from either the municipal registry of persons or their general practitioner.

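### PARIS joint models: AAA diameter and growth enter as ordinary covariables with no fixed time window, which can bias the hazard ratios

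*Protocol article*

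**What the plan says.** The PARIS analysis is set out in the protocol article, Table 5 (Ethics and dissemination), in the row on statistical analysis. One joint model is planned per biomarker: "joint modelling combines linear mixed-effects models for the estimation of slope of temporal change per biomarker with Cox regression", with rupture and all-cause mortality as the events. The biomarker terms are specified: "The estimated slope and value of the studied biomarker will be added as covariables in each joint model".

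Diameter has a different role. The row says that "both models will be adjusted for potentially relevant covariables, including but not limited to sex, age, most recent AAA diameter and cardiovascular comorbidity", chosen by forward selection at p < 0.05. The next sentence exchanges one term: "In addition, AAA growth instead of the most recent AAA diameter will be analysed in a separate multivariable joint model".

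Growth is defined only earlier in the same row: "Individual AAA growth (based on repeated AAA diameter measurements) and the evolution of serum levels of cytokines and proteases will each be analysed with linear" (the sentence goes on to name mixed models, which yield a slope). No time window is given for that slope, or for which diameter counts as most recent.

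Under Study procedures, guideline visits take place "at intervals of 2 years, 1 year or 3 months, depending on the AAA diameter", and only images from routine care are stored. The Statistical analyses section names landmarking beside joint models as a way to study rupture.

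**The concern.** A joint model is used when a marker is internal to the patient, measured with error at scattered visits, and cut off by the event. Such a marker should not enter a Cox model as if it were known at all times. The plan applies this reasoning to the biomarker. Diameter is the same kind of variable, yet it stands in the list with sex and age.

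Two separate problems can follow:

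- **Growth.** One slope per patient from all diameters uses, for everyone still at risk at time t, measurements made after t. A patient who ruptures early has few diameters, so the predicted slope is pulled towards the mean. Patients followed for longer keep more of their own slope.
- **Diameter.** One last value per patient is larger in those who survive longer, simply because the aneurysm had more time to grow. If the value is instead carried forward to t, it is noisy and may be up to 2 years old.

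At stake are the hazard ratio for growth or diameter and, through incomplete or distorted adjustment, the biomarker hazard ratios that these models are meant to deliver.

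**Working it through.** **Step 1: the text.** Table 5 describes a longitudinal part for the biomarker only. Diameter is an adjustment term, and growth takes its place. No second longitudinal submodel is described. The plan gives no figure for these models that could be reproduced. Its sample size of 750 belongs to the correlation analysis and does not enter here.

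**Step 2: growth as one whole-follow-up slope.** All inputs are assumptions: annual diameters, growth SD 1.5 mm/yr, measurement SD 2 to 3 mm, baseline rupture hazard 1% per year, death 5% per year. Hazard ratios are per SD of growth.

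| Setting | True HR | HR from whole-follow-up mixed-model slope |
|---|---|---|
| Exit at 55 mm, three implementations | about 2.0 | 1.23–1.34, 1.34–1.43, 1.28–1.37 |
| Exit at 55 mm, diameter-dependent visits | 2 | about 1.1–1.2 |
| Exit at 55 mm | 1.5 | 1.09–1.19, 1.18–1.24 |
| No exit at 55 mm | 1.98 | 1.50–1.58 |
| No exit at 55 mm | 1.50 | 1.28–1.32 |
| No growth effect, linear growth | 1 | 0.97–1.03 |

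On the log scale, for the implementation in which Cox regression on true growth gave 2.07–2.09, the share retained with exit at 55 mm lies between ln 1.34 / ln 2.09 = 0.40 and ln 1.43 / ln 2.07 = 0.49. Without that exit it is ln 1.50 / ln 1.98 = 0.59 to ln 1.58 / ln 1.98 = 0.67.

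With exit at 55 mm and variance components taken as known, slopes using only data up to t gave 1.93–1.95 for a true value of about 2.0.

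In the cell with diameter-dependent visits, the biomarker log HR rose from about 0.28 to 0.35–0.49. As hazard ratios, exp(0.28) = 1.32 became exp(0.35) = 1.42 to exp(0.49) = 1.63.

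**Step 3: diameter.** A separate simulation assumed baseline diameter 42 (SD 5) mm, growth 2.2 (SD 1.5) mm/yr, diameter–biomarker correlation 0.4, a true biomarker log HR of 0.30 and a true diameter log HR of 0.08 per mm unless stated. The true biomarker was supplied, so only the handling of diameter or growth varied.

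| Handling of diameter | Biomarker log HR | Diameter log HR per mm |
|---|---|---|
| True diameter at t (reference) | 0.304 | 0.077 |
| Carried forward to t | 0.307–0.317 | 0.071 (annual visits), 0.073 (2-yearly), 0.078 (measurement SD 1.5 mm) |
| Carried forward to t, exit at 55 mm (reference 0.301; 0.077) | 0.323 | 0.062 |
| One fixed last diameter | 0.414–0.415 | about −0.006 |
| One fixed last diameter, exit at 55 mm | 0.446 | −0.054 |
| One fixed last diameter, true diameter effect nil | 0.452 | −0.053 |

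Carrying forward lowers the diameter coefficient by at most 1 − 0.071/0.077 = 8% without the exit, and by 1 − 0.062/0.077, about 20%, with it. The biomarker coefficient rises by 0.307/0.304 = 1% to 0.323/0.301 = 7%. A fixed last diameter removes or reverses the diameter effect.

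At correlation 0.16 the biomarker coefficient barely moved: 0.300 with diameter carried forward and 0.300 with a fixed last diameter, against 0.302. The fixed last diameter still took the diameter coefficient from 0.078 to 0.001.

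**Step 4: limits of the growth result.** In the Step 3 simulation with no diameter effect, linear growth gave a growth coefficient of −0.017 (SE 0.013), so no clear bias. Accelerating growth (0.15 mm/yr²) gave −0.36 and a biomarker coefficient of 0.39. Slopes up to t, with the curvature treated as known, gave −0.017 and 0.307.

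Where rupture depended on current diameter and not on growth itself, the whole-follow-up slope matched true growth without the exit (0.358 against 0.360) and fell short with it (0.140 against 0.184). Slopes up to t then gave 0.485 and 0.280, since growth is only a stand-in for diameter in that case. Bias is therefore not universal.

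**The case against.** The strongest reply is that the article nowhere says later measurements will be used. A reader might infer from the growth definition that they will, but the text leaves the window open. A window alone is the kind of detail an article may leave to a fuller document. The phrase about a separate multivariable joint model could even mean that growth gets its own longitudinal submodel, which would be the remedy. Landmarking is already named as an alternative for rupture.

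It can also be said that diameter is only an adjustment term, kept only if selected. With linear growth and no effect, no false association appears. At a correlation of 0.16, the value used for the sample size (there between biomarker levels and growth), the biomarker coefficient hardly moves.

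Most of this stands, and it limits the point to a conditional one. It does not remove it. The role given to diameter is stated, and putting growth in its place gives growth the same role. Nothing in Table 5 describes a second submodel. The readings left open run from minor to severe bias.

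Two further inferences should be resisted. Growth is not the central exposure: Table 5 lists it as a primary outcome, and the exposures are the serum proteases and cytokines. Nor would patients with a single diameter be lost, since the planned mixed models retain them.

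**Conclusion.** The point holds in conditional form. The plan protects the biomarker against measurement error and endogeneity but leaves diameter and growth as plain covariables, with no rule on which measurements count at time t.

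If one whole-follow-up slope is used, a true growth hazard ratio of about 2.0 may be reported as about 1.1 to 1.4 with exit at 55 mm, or 1.50 to 1.58 without it. The biomarker hazard ratio can be inflated when biomarker and growth are correlated. A single last diameter per patient can remove or reverse the diameter effect. If diameter is carried forward to t, the bias is modest: up to 8% on the diameter log hazard ratio, about 20% with exit at 55 mm, and 1 to 7% on the biomarker.

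Every size rests on assumed growth, error, visit and event rates, because the documents supply none. The conclusion that hazard ratios will be biased, or that future data will be used, goes further than the text allows. The change is still worth making, because the wording permits the harmful reading.

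**What to change.** Amend the statistical analysis row of Table 5, and the protocol or analysis plan behind it, so that each joint model has two longitudinal submodels, one for the biomarker and one for AAA diameter. Link rupture and death to the current value of diameter in the main model and to its current slope in the growth model. These links replace both the most recent diameter and growth as covariables. Let the diameter submodel allow for non-linear growth.

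If two submodels cannot be fitted, use the landmark model named under Statistical analyses. State that diameter and slope at each landmark are estimated only from measurements made up to that landmark.

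The cost is analysis wording, more computing per biomarker, and possible convergence difficulty with few ruptures. No new data are needed. If the change counts as a significant modification, the article's own rule requires a formal amendment approved by both ethics boards. Completion is expected in October 2032, so there is time.
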